### Data collection procedures and measures

Participants complete self-report measures via REDCap at baseline (prior to starting the treatment/wait-list period) and at post-treatment/wait-list after completing the six-session intervention group or 6-week wait period. For data capture and storage, this study uses REDCap, a secure, password-protected, and HIPAA compliant web-based data platform hosted by the UW Institute of Translational Health Sciences [29, 30].

The primary and secondary outcomes are listed in Table 1. Primary outcomes include the Feasibility of Intervention Measure (FIM), Acceptability of Intervention Measure (AIM), and Intervention Appropriateness Measure (IAM) [20]. Each measure consists of four items that are rated on a 5-point ordinal scale assessing the degree to which an intervention is feasible (e.g., “this intervention seems doable”), agreeable (e.g., “I like this intervention”), or appropriate (e.g., “this intervention seems fitting”). A score greater than 3 (“neither agree nor disagree”) will be used as the cutoff for a dichotomous rating of feasibility, acceptability, and appropriateness. The FIM, AIM, and IAM have shown excellent reliability as well as substantive and discriminant content validity [20]. Secondary outcomes include Patient-Reported Outcomes Measurement Information System (PROMIS) measures of fatigue, sleep disturbance, cognitive difficulties, self-efficacy, pain interference, depression and anxiety symptoms [21], and a long COVID symptom and impact tools measure [22] and Patient Global Impression of Change scale [24].

In addition, participants randomized to the self-management intervention (*n* = 25) complete a 45-minute semi-structured interview with research staff within one month after the final session. The interviewer queries participants about the feasibility, acceptability, and appropriateness of the intervention as well as suggestions for improving the intervention across these areas. Participants are also asked about the perceived efficacy of the intervention and how the intervention could be improved to increase efficacy. Last, the interviewer queries participants’ impressions of the intervention workbook and elicit suggestions for improvement. Data is transcribed via Rev, a secure online transcription service [31].

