**Methods:**

This pilot trial (*N* = 50) uses a pragmatic, randomized two-group parallel design set within the University of Washington Post-COVID Rehabilitation and Recovery Clinic. The self-management intervention is a 6-week, group-based telemedicine intervention that teaches evidence-based strategies to manage common symptoms and improve stress management as well as communication and self-advocacy. The comparator is a wait-list control. Participants complete self-report measures of the primary and secondary outcomes at baseline and post-treatment/wait-list. Primary outcomes include intervention feasibility, acceptability, and appropriateness. Secondary outcomes include Patient-Reported Outcomes Measurement Information System measures of fatigue, sleep disturbance, cognitive difficulties, self-efficacy, pain interference, depression and anxiety symptoms, and a measure of long COVID symptoms and impression of change. At post-intervention, intervention participants also complete a qualitative interview to inform intervention refinement. Quantitative data will be examined using descriptive and statistical analysis including *t*-tests and chi-square tests to compare the intervention and wait-list groups on secondary outcomes. Qualitative data will be analyzed using the rigorous and accelerated data reduction technique (RADaR).

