** Secondary outcomes**			
Depression Short Form 8b** [21]		X	X
Anxiety Short Form 8a** [21]		X	X
Fatigue Short Form 8a** [21]		X	X
Sleep Disturbance Short Form 8a** [21]		X	X
Cognitive Function — Abilities Short Form 8a** [21]		X	X
Self-Efficacy for Managing Chronic Conditions — Managing Symptoms Short Form 8a** [21]		X	X
Ability to Participate in Social Roles and Activities Short Form 8a** [21]		X	X
Pain Interference Short Form 8a** [21]		X	X
Long COVID symptom and impact tools [22]		X	X
Credibility/expectancy questionnaire [23]		X*	
Patient Global Impression of Change scale [24]			X*

^*^Completed by intervention participants only

**Patient-Reported Outcomes Measurement Information System (PROMIS)

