### Statistical analysis plan

An intent-to-treat (ITT) approach will be used for all quantitative analyses. If participants are missing data at the individual-item level of a multi-item scale, we will impute the missing data using the within-group mean scores for the scale; however, a score will not be imputed if the participant is missing ≥ 40% data in a scale.

First, we will compute descriptive statistics to characterize the sample in terms of demographic and condition-related factors. To assess the first study aim, we will calculate the means and standard deviations of the AIM, IAM, and FIM and quantify the proportion of participants who rate the intervention as feasible, acceptable, and appropriate (average score greater than 3). We will quantify adherence as the percentage of sessions attended out of six sessions. These statistics will be used to contextualize the qualitative results and help inform the extent of modifications necessary to improve the feasibility, acceptability, and appropriateness of the intervention for adults with long COVID.

The second study aim to examine intervention effects is exploratory. We will determine whether randomization was successful by using *t*-tests and chi-square tests to compare the intervention and wait-list groups on a variety of demographic and baseline outcome variables. Any variables that differ between the groups will be included as covariates in the subsequent regression models. After examining randomization, we will explore intervention effects. For the second aim, we will conduct linear regression to assess intervention effects on each outcome (nine models) and will covary for the baseline level of the outcome variable, intervention credibility/expectancy [23], age, sex, and race.

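### The abstract promises a between-arm comparison of impression of change that Table 1 makes impossible, and names different tests from the analysis section

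*Protocol article*

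**What the plan says.** All references are to the protocol article.

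- **Abstract, Methods.** Impression of change is listed among the secondary outcomes. The quantitative analysis is said to include t-tests and "chi-square tests to compare the intervention and wait-list groups on secondary outcomes".
- **Data collection procedures and measures.** The section opens by deferring to the table: "The primary and secondary outcomes are listed in Table 1". It then names PROMIS "measures of fatigue, sleep disturbance, cognitive difficulties, self-efficacy, pain interference, depression and anxiety symptoms [21", followed by "and a long COVID symptom and impact tools measure [22] and Patient Global Impression of Change scale [24".
- **Table 1.** Eleven rows stand under secondary outcomes. PGIC has one mark, at the post-treatment time point, with an asterisk. Credibility/expectancy has one mark, at baseline, with the same asterisk. The footnote reads "Completed by intervention participants only". The table also lists "Ability to Participate in Social Roles and Activities Short Form 8a", collected before and after in both arms and absent from the text list and the abstract.
- **Statistical analysis plan.** For the second aim, "we will conduct linear regression to assess intervention effects on each outcome (nine models". The models "will covary for the baseline level of the outcome variable, intervention credibility/expectancy [23], age, sex, and race". T-tests and chi-square tests appear here only to check whether randomization balanced demographic and baseline variables. The nine outcomes are not named.

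**The concern.** The second aim is comparative: it hypothesises greater improvement in the intervention arm than on the wait-list. An outcome recorded in one arm cannot address that aim, because treatment effect and spontaneous change are mixed in a single set of ratings. A reader of the abstract would nevertheless expect a between-arm result for impression of change.

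The abstract and the analysis section also give different methods for the same comparison. An unadjusted test and a baseline-adjusted regression differ in precision. With about 20 completers per arm expected, that difference could affect which exploratory signals appear.

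Finally, the regression that should replace the abstract's tests uses a covariate that is itself collected in one arm only.

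**Working it through.** **1. Reproduce the figure of nine models.** From Table 1:

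| Collected | Measures | Count |
|---|---|---|
| Both arms, baseline and post | 8 PROMIS short forms + long COVID tool | 9 |
| Intervention arm, baseline only | Credibility/expectancy | 1 |
| Intervention arm, post only | PGIC | 1 |
| Total secondary rows | | 11 |

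The two-arm measures with a baseline number 8 + 1 = 9, which reproduces the plan's figure.

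**2. Count the text list.** Fatigue, sleep disturbance, cognition, self-efficacy, pain interference, depression and anxiety make 7. Adding the long COVID tool and PGIC gives 7 + 1 + 1 = 9. The two sets share 8 outcomes. The text has PGIC where Table 1 has social roles, so only 8 of the text's 9 can be modelled as specified.

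**3. Can PGIC be compared between arms?** Every participant with a PGIC score has arm = 1, so the arm column equals the intercept and its coefficient is not identified. A rank check with simulated covariates (intercept, arm, baseline, age, sex, race as one indicator: 6 columns) gives rank 6 with both arms present. With intervention-arm rows only, it gives rank 5 of 6, at 20 and at 25 per arm. PGIC also has no baseline score to adjust for. A t-test or chi-square test fails for the same reason: there is no second group.

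**4. Does the regression work for the other nine?** Adding credibility/expectancy makes 7 columns. The value is absent by design for the whole wait-list arm, so complete cases are 25 of 50 (or 20 of 40 completers) with 0 wait-list participants, and the rank is 6 of 7. The arm effect is again not estimable. Imputation would not rescue it from data, because no wait-list value is ever observed.

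**5. What the choice of test costs.** The documents give no baseline-to-outcome correlation r, so 0.5 to 0.7 is assumed. The comparator is regression adjusted for baseline alone, with equal variances before and after.

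- Post-score t-test against adjusted regression: variance ratio 1/(1 − r²)
- Change-score t-test against adjusted regression: 2(1 − r)/(1 − r²) = 2/(1 + r)

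| r | Post-score | Change-score |
|---|---|---|
| 0.5 | 1/0.75 = 1.33 | 2/1.5 = 1.33 |
| 0.6 | 1/0.64 = 1.56 | 2/1.6 = 1.25 |
| 0.7 | 1/0.51 = 1.96 | 2/1.7 = 1.18 |

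The abstract does not say whether the t-test is on post scores or on change.

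**The case against.** A reader might infer that the number nine is wrong, or that the modelled set is so open that outcomes could be added or dropped after the data are seen. The documents do not support either reading. The text defers to Table 1, and its own list is introduced in a way that need not be exhaustive. The models require a baseline value, and exactly nine Table 1 measures have one in both arms. PGIC does not fit that description. Social roles is prospectively listed in Table 1 as a secondary outcome, so its absence from the prose looks like an editorial slip.

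It can also be said that the analysis section never states that PGIC will be regressed, and that a secondary outcome may properly be described in one arm. That stands: only the abstract implies the comparison. The abstract may have merged the randomization check with the effect analysis, and the dedicated section is the more specific of the two. That makes the conflict easy to resolve, but it does not remove it.

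The upper variance ratio of 1.96 should not be read as the cost of following the abstract. It needs both r = 0.7 and a post-score test. The hypothesis is about change from before to after, so a change-score test is at least as natural a reading, and there the ratio at r = 0.7 is 1.18.

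Lastly, assessments were expected to finish by February 2024, so new wait-list collection may reach few participants or none.

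**Conclusion.** The point holds in a limited form. One comparison implied by the abstract, impression of change between arms, cannot be made with the data in Table 1. The abstract's tests conflict with the analysis section's regression. The nine models are sound as a count and correspond to Table 1's two-arm measures; the text list should be brought into line with them.

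The most consequential mismatch of this kind is credibility/expectancy. As written and fitted on complete cases, none of the nine models can estimate an arm effect.

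Severity is modest, because the second aim is declared exploratory and the primary outcomes are unaffected. The conclusions on PGIC and the covariate follow from the data schedule and need no assumed figure. Only the precision cost of an unadjusted test, 1.18 to 1.96 in variance across both readings, depends on an assumed correlation.

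**What to change.** - **PGIC.** Add it to the wait-list arm's automated 6-week survey, worded as change since baseline, and compare arms without a baseline term. The cost is one extra item for wait-list participants. Where collection is complete, report PGIC descriptively in the intervention arm and take it off the comparative outcomes; this costs only wording.
- **Outcome list.** Name the nine modelled outcomes as the eight PROMIS forms in Table 1 plus the long COVID tool, and add social roles to the text and the abstract.
- **Abstract.** Replace the t-tests and chi-square tests for secondary outcomes with baseline-adjusted linear regression, and keep those tests for the randomization check.
- **Credibility/expectancy.** Drop it from the between-arm models or collect it in both arms. Dropping costs nothing in data and is the only option once baseline collection has ended. If it is collected in both arms, note that the baseline battery follows randomization, so knowledge of allocation could influence the answers.

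The article states that the analysis has not yet been done, so these corrections can be made and dated before it begins.

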### Data and safety monitoring

The principal investigators provide oversight of the trial in collaboration with study staff to assure adequate protection of the rights of human subjects. They monitor progress of the project, protocol adherence, substantial protocol amendments, and participant safety including adverse events on an ongoing basis in weekly meetings and submit a report to the IRB twice annually. Because this study does not use investigational drugs or devices and poses minimal risk to participants, a data and safety monitoring board, which is required for most United States Food and Drug Administration studies, was not deemed necessary. Instead, the above process serves two purposes: it accommodates the expected low-base rate of problems and allows for the earlier identification of issues more appropriately than a data and safety monitoring board that would meet at an arbitrary regular interval. Likewise, there is no auditing process in place beyond the IRB standard procedures of potentially conducting an audit during the course of the research or after the project is completed. Regarding provisions for ancillary and posttrial care, participants in the self-management group are passively monitored for suicidal ideation. If a group member reports suicidal ideation, the licensed psychologist leading the group provides appropriate follow-up including risk assessment, safety planning, and provision of resources depending on level of risk.

*Note: Future tense will be used from now until the*
Discussion*section, as we have yet to conduct the statistical analysis plan*

We will make the data and associated documentation available to users only under a data-sharing agreement that provides for the following: (1) a commitment to using the data only for research purposes and not to identify any individual participant, (2) a commitment to securing the data using appropriate computer technology, and (3) a commitment to destroying or returning the data after analyses are completed.

### Statistical analysis plan

An intent-to-treat (ITT) approach will be used for all quantitative analyses. If participants are missing data at the individual-item level of a multi-item scale, we will impute the missing data using the within-group mean scores for the scale; however, a score will not be imputed if the participant is missing ≥ 40% data in a scale.

First, we will compute descriptive statistics to characterize the sample in terms of demographic and condition-related factors. To assess the first study aim, we will calculate the means and standard deviations of the AIM, IAM, and FIM and quantify the proportion of participants who rate the intervention as feasible, acceptable, and appropriate (average score greater than 3). We will quantify adherence as the percentage of sessions attended out of six sessions. These statistics will be used to contextualize the qualitative results and help inform the extent of modifications necessary to improve the feasibility, acceptability, and appropriateness of the intervention for adults with long COVID.

The second study aim to examine intervention effects is exploratory. We will determine whether randomization was successful by using *t*-tests and chi-square tests to compare the intervention and wait-list groups on a variety of demographic and baseline outcome variables. Any variables that differ between the groups will be included as covariates in the subsequent regression models. After examining randomization, we will explore intervention effects. For the second aim, we will conduct linear regression to assess intervention effects on each outcome (nine models) and will covary for the baseline level of the outcome variable, intervention credibility/expectancy [23], age, sex, and race.

For the third aim, we will analyze qualitative data using the rigorous and accelerated data reduction (RADaR) technique [32]. The RADaR technique involves identifying an overarching research question, developing an all-inclusive data table from interview transcripts, and revising the table to reduce the data by retaining only the data that can answer the research question. This overall process is completed for each research question. The overarching research questions for this qualitative analysis are as follows: what do participants like about the long COVID group intervention and the participant workbook, what do they dislike about the long COVID group intervention and the participant workbook, and what are their suggestions to improve the intervention’s feasibility, acceptability, appropriateness, and efficacy? Qualitative findings will contextualize the primary outcomes data to inform specific modifications to improve the feasibility, acceptability, and appropriateness of the intervention.

We will independently and collectively review interview transcripts. Step 1 of the RADaR technique (transcription) will be completed by Rev, a HIPAA-compliant online transcription service [31]. Then a research team member will complete Step 2 of combining the individual transcripts to create an all-inclusive data table. We will complete Step 3 individually to reduce the data to a more concise data table that answers a single research question and includes notes and preliminary codes. We will then review, compare, and discuss the Step 3 data tables to select which text chunks will move forward in the analysis of the particular research question and to develop consensus on codes that will likely remain in the code column throughout subsequent steps and inform subsequent theme discussion and identification. A research team member will produce a revised data table based on the team consensus from the meeting. This process will be repeated (i.e., repeat Step 3 individually and discuss the data tables to achieve consensus) and generate and refine themes related to the research question as many times as necessary to agree the remaining data is sufficient for answering the particular research question. We will repeat the RADaR technique for each research question. We will then produce a report for each question that contains themes and exemplar quotes to help guide intervention refinement. Rigor for the RADaR technique is achieved by mapping the information in each data table phase between the individual team members and across the data table reduction phases. Thus, the iterative process involves close assessment of each analyst’s reviewing, reducing, and coding styles. Additionally, we will adhere to the standards for reporting qualitative research throughout data collection, analysis, synthesis, and interpretation and report these standards in the resultant manuscript [33]. Trial results will be disseminated via presentation at local and national conferences, peer-reviewed manuscript publications, and reporting on ClinicalTrials.gov.

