### Study setting

This trial aims to enroll and randomize 50 participants who receive care at the UW Post-COVID Rehabilitation and Recovery Clinic within the state of Washington. This is a high-demand outpatient clinic housed within an AMC that has served over 2500 patients since opening in 2020. Assuming a 10% dropout rate, a total of 50 participants will yield 20 completers in each study condition. This sample size was selected to characterize the intervention’s feasibility, acceptability, appropriateness, and preliminary efficacy to inform intervention improvement. A sample size of 20 participants in each condition (accounting for attrition) is appropriate given the specificity of our qualitative research questions [25, 26]. Likewise, this sample size is appropriate for estimating the proportion of participants who rate the intervention as feasible, acceptable, and appropriate. The lower bound of the 95% CI will be above 60% if at least 17 out of 20 (85%) of intervention participants rate the intervention as feasible, acceptable, or appropriate (Supplemental Fig. 1), which is a conservative estimate given satisfaction ratings for similar rehabilitation interventions [27].

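### Aim 2 is labelled intent-to-treat, but the stated scoring rule and regression leave out randomised participants with no post-treatment survey, so it is an available-case analysis by assigned arm

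*Protocol article*

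**What the plan says.** All statements below are in the protocol article.

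- **Analysis principle** (Statistical analysis plan): "An intent-to-treat (ITT) approach will be used for all quantitative analyses".
- **Missing items** (same section): "If participants are missing data at the individual-item level of a multi-item scale, we will impute the missing data using the within-group mean scores".
- **Limit on that rule** (same section): "a score will not be imputed if the participant is missing ≥ 40% data in a scale".
- **Aim 2 model** (same section): "we will conduct linear regression to assess intervention effects on each outcome (nine models"), adjusted for the baseline value of the outcome and other covariates.
- **Status of Aim 2** (same section): "The second study aim to examine intervention effects is exploratory".
- **Assessment times** (Data collection procedures and measures): "Participants complete self-report measures via REDCap at baseline (prior to starting the treatment/wait-list period) and at post-treatment/wait-list". Table 1 likewise shows a single assessment after allocation.
- **Expected loss** (Study setting): "Assuming a 10% dropout rate, a total of 50 participants will yield 20 completers in each study condition".

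No sentence says outright that participants without a post-treatment survey are excluded, and none gives a method for a questionnaire that is missing altogether. The section Randomization and procedures to minimize bias says that REDCap issues the survey links automatically. It attaches no attendance condition.

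**The concern.** An intent-to-treat label applied to every quantitative analysis tells the reader that all 50 randomised participants count in the comparison, each in the assigned arm. The rule and the model that follow keep the second half of that promise but not the first. Someone who does not answer the post-treatment survey is missing 100% of every scale, so the rule yields no score. A regression on one post-treatment value has no other follow-up from which that person could contribute.

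What is at stake is how the result can be described. Readers would take the Aim 2 estimates, which feed into intervention refinement and further testing, as covering everyone randomised. In fact they would rest on those who returned the survey. If non-return is related to how participants fared, the comparison no longer has the protection of randomisation, and the label would hide this.

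**Working it through.** **1. The article's loss figures.** Inputs from Study setting and the randomisation section: 50 participants, 1:1 (25 per arm), 10% dropout, 20 completers per arm.

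- 10% dropout: 50 × 0.90 = 45 remain (22.5 per arm), so 5 are lost.
- 20 completers per arm: 2 × 20 = 40 remain, so 10 are lost. The implied dropout is 1 − 20/25 = 20%.

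The stated 20 per arm does not follow from the stated 10%. That mismatch is a separate matter. Here it means only that the article supports a range of p = 0.10 to 0.20 for the fraction without outcomes.

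**2. The scoring rule.**

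| Scale | Missing items | % missing | Scored? |
|---|---|---|---|
| 8 items | 3 | 37.5 | yes |
| 8 items | 4 | 50 | no |
| 8 items | 8 (no survey) | 100 | no |

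The PROMIS forms in Table 1 are 8-item short forms. An unreturned survey is never scored.

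**3. The model.** Each of the nine regressions has one post-treatment score as its outcome. Without that score the record drops out. So 45 of 50 (p = 0.10) or 40 of 50 (p = 0.20) enter. These counts assume that covariates are available in both arms. Table 1 marks the credibility/expectancy covariate as collected in the intervention arm only, which is a different problem and is set aside here.

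**4. Possible size of bias.** The article gives no effect size and no reason for non-return, so everything in this step rests on assumptions.

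Let participants with missing outcomes fare worse than observed ones in the same arm by δ_I (intervention) or δ_W (wait-list), in SD units, with missing fractions p_I and p_W. Then

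overstatement = p_I × δ_I − p_W × δ_W.

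- *Missing intervention participants gained nothing, wait-list losses ignorable.* All-randomised effect = (1 − p) × observed effect, so the ratio of observed to all-randomised is 1/(1 − p): 1/0.90 = 1.11 and 1/0.80 = 1.25. With an illustrative observed effect of 0.50 SD, the all-randomised effect is 0.45 or 0.40 SD.
- *δ_I from 0.25 to 1.0 SD, wait-list losses ignorable.* Overstatement is 0.10 × 0.25 = 0.025 to 0.10 × 1.0 = 0.10 SD at 10% missing, and 0.20 × 0.25 = 0.05 to 0.20 × 1.0 = 0.20 SD at 20%.
- *Equal loss and equal δ in both arms,* for example 0.50 SD: 0.10 × 0.50 − 0.10 × 0.50 = 0.
- *Selective loss in the wait-list arm only:* 0 − 0.10 × 0.50 = −0.05 SD, an understatement.

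The sign therefore depends on facts that the article does not supply.

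**5. Scale against noise.** The unadjusted standard error of a two-arm difference with 45 people is about 2/√45 = 0.30 SD. A shift of 0.05 SD (10% missing, 0.50 SD effect, no gain in the missing) is about 0.05/0.30, or one-sixth, of a standard error.

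**The case against.** The strongest reply is that the exclusion is inferred and nowhere written. The 40% clause qualifies a sentence about gaps at item level, so it reads as a scoring rule. Whole missing assessments may be handled in a fuller protocol or analysis plan that is not shown. This has weight, and silence alone would be no fault in a condensed article. But the article is not merely silent. It claims a property for all quantitative analyses and then fixes a rule and a model that do not deliver it. A further method would have to be added before the label fits.

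A reader might go further and call Aim 2 a completer analysis. The documents do not support that. Survey links go out automatically, attendance is only summarised as adherence, and no attendance-based exclusion is stated. Someone who misses sessions but returns the survey stays in the assigned arm. The mention of completers in Study setting is a sample-size assumption and does not define an analysis set.

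A reader might also infer that the effect will be inflated by 11% to 25%. That too goes beyond the text. Nothing links non-return to benefit, loss is planned for in both conditions, and the factor only restates the assumption of no gain among the missing.

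Two objections to possible remedies stand as well. A mixed model for baseline and post-treatment scores gains almost nothing from people who have only a baseline. Imputing within arm from nine baseline scales, age, sex and attendance would mean 12 predictors for about 20 to 22 observed people, which is fragile. Finally, Aim 2 is declared exploratory, so no confirmatory claim is at risk.

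**Conclusion.** The point holds in a limited form. As written, Aim 2 includes randomised participants with available outcomes, analysed by assigned arm. It does not include all randomised, and the blanket intent-to-treat label is inaccurate for it. About 5 to 10 of 50 would be left out, depending on which of the article's two loss figures is used.

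The direction and size of any bias are unknown. The factor of 1.11 to 1.25 holds only if missing intervention participants gained nothing and wait-list losses are ignorable. At the stated 10% dropout the illustrative shift is small beside the sampling error. The change is worth making because it alters what the result may claim and costs little. The defect does not undermine the pilot.

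**What to change.** 1. Describe the Aim 2 analysis set as all randomised participants with an available outcome, analysed by assigned arm, in place of the general intent-to-treat statement. Report the number missing by arm for each outcome.
2. State that the post-treatment survey is sent to everyone randomised, whatever their attendance. The data-collection section times it after completion of the six-session group, which could be misread as a condition.
3. Add one sensitivity analysis that keeps all 50. Multiply impute missing post-treatment scores from a small predictor set: the baseline of that outcome and, in the intervention arm, sessions attended. Repeat it with missing intervention-arm outcomes drawn from the wait-list distribution, because only that version probes the case in which non-returners did not benefit. Baseline surveys are completed after randomisation, so any missing baseline value would need imputing in the same step.

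The cost is a few sentences and slightly more analysis, with no extra participants. The sensitivity estimate may be less favourable than the main one.

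### Missing items are filled with the group mean instead of the participant's own answers, which can tip a neutral or mildly negative rater over the primary cutoff

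*Protocol article*

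**What the plan says.** The Statistical analysis plan section of the protocol article fixes one rule for item-level missing data on every multi-item scale: "we will impute the missing data using the within-group mean scores for the scale". The only limit is that "a score will not be imputed if the participant is missing ≥ 40% data in a scale". No other section gives a different rule or a sensitivity analysis for missing items.

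The primary outcomes are the AIM, IAM and FIM. Under Data collection procedures and measures, "Each measure consists of four items that are rated on a 5-point ordinal scale", and 3 is the neutral response. A participant counts as positive when the average exceeds 3. The footnote to Table 1 marks these measures "Completed by intervention participants only". The sample-size reasoning under Study setting takes 20 completers per condition and states that 17 positive ratings out of 20 (85%) place the lower 95% confidence limit above 60%.

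The secondary outcomes include eight PROMIS short forms labelled 8a or 8b. Outcomes are compared between arms by linear regression, under an aim that the article calls exploratory.

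**The concern.** On a multi-item scale, the best evidence about a skipped item is what the same person answered on the others. The planned rule discards it and inserts what other people answered, which pulls every incomplete score toward the group average.

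This matters most where a score is cut at a threshold. If the group as a whole is favourable, a participant at or just below neutral can be carried over the cutoff by other participants' opinions. The primary result is a proportion among about 20 people, so one such case is visible.

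On the secondary scales the filled values are treated as observed although they carry no individual variation. Within-arm spread, and with it the standard error of the arm comparison, is understated.

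**Working it through.** **Inputs from the article.** Four items scored 1–5; positive if the average is above 3; no filling at 40% or more missing; 20 completers per arm; 17/20 said to give a lower limit above 60%.

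**Assumptions.** The article gives no group mean, item-missingness rate or inter-item correlation. 'Group' is read as study arm, and the fill value as that arm's mean item score. Eight items per PROMIS form is inferred from the form names.

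**1. The plan's own figure.** At 17/20 the lower 95% limit is 62.1% (Clopper-Pearson), 64.0% (Wilson), 63.1% (Agresti-Coull), 65.1% (Jeffreys) or 69.4% (Wald). All exceed 60%, so the statement is reproduced. At 16/20 the limits are 56.3%, 58.4%, 57.8%, 59.2% and 62.5%. Seventeen is therefore the smallest count that clears 60% by every method except Wald.

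**2. How many items can be filled.** On four items, 1/4 = 25% is allowed and 2/4 = 50% is not: at most one item. On eight items, 3/8 = 37.5% is allowed and 4/8 = 50% is not: at most three.

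**3. Who crosses the primary cutoff.** Let s be the sum of the three answered items and g the group mean. The planned score is (s + g)/4; the participant's own mean is s/3.

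| s | Own mean | Planned score above 3 when | Example |
|---|---|---|---|
| 9 | 3.00, not positive | g > 3 | g = 3.5: 12.5/4 = 3.125; g = 4.2: 13.2/4 = 3.30 |
| 8 | 2.67, not positive | g > 4 | g = 4.2: 12.2/4 = 3.05 |
| 7 or less | at most 2.33, not positive | never | at most (7 + 5)/4 = 3.00 |
| 10 | 3.33, positive | g > 2 | falls to 3.00 or below only if g ≤ 2 |

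Unless the group mean is 2 or lower, the error runs in one direction only, toward a positive rating.

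**4. Size on the primary proportion.** One reclassified participant in 20 is 1/20 = 5 percentage points. From 16/20 to 17/20 the Clopper-Pearson lower limit moves from 56.3% to 62.1%.

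**5. How often.** In an illustrative simulation (n = 20, group mean about 3.75–3.93, 77–83% truly positive, items missing at random), the chance of at least one upward reclassification on a given scale, relative to own-mean scoring, was:

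| Items missing | Chance per scale |
|---|---|
| 1% | 7–8% |
| 2% | 14–15% |
| 5% | 29–32% |
| 10% | 44–47% |

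**6. Secondary scales.** Take eight items with unit variance and inter-item correlation ρ = 0.6. Complete-data score variance is ρ + (1 − ρ)/8 = 0.65. With k items set to a constant it is ((8 − k)/8)² × [ρ + (1 − ρ)/(8 − k)]:

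- k = 1: 0.766 × 0.657 = 0.503, ratio to complete data 0.774
- k = 2: 0.5625 × 0.667 = 0.375, ratio 0.577
- k = 3: 0.391 × 0.680 = 0.266, ratio 0.409

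If a fraction f of participants is affected, the arm variance ratio is f × ratio + (1 − f), and the SD ratio is its square root:

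- f = 10%, k = 1: 0.977, SD −1%
- f = 10%, k = 2: 0.958, SD −2%
- f = 20%, k = 3: 0.882, SD −6%
- f = 40%, k = 3: 0.763, SD −13%

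In simulations with 20 per arm and an unadjusted t-test, type I error stays at about 5% with one or two items missing in 5–10% of participants. It is about 7% with three items missing in 20%, and 9–10% with three missing in 40%. In the two heavy settings, own-mean scoring stays at the complete-data level (4.9% against 4.8%, and 5.6% against 5.6%).

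**The case against.** The case for leaving the rule alone is mainly one of size, and much of it stands.

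- **Few people are exposed.** Reclassification needs exactly one missing item and an answered sum of exactly 9 or 8. A reader might infer that negative raters in general become positive. The arithmetic rules this out: a sum of 7 or less cannot cross.
- **60% is not a pass mark.** A reader might treat 16/20 to 17/20 as crossing a success criterion. The article uses the 60% bound to justify precision, and says the ratings will put the qualitative findings in context and guide modifications. The harm is to a descriptive proportion.
- **Allocation cannot leak into the primary measures.** Only the intervention arm completes them. That each arm is filled with its own mean matters only for the secondary comparison.
- **Secondary p-values are not shown to be wrong.** A reader might infer clearly inflated type I error. That needs three missing items in a fifth or more of participants, and the article gives no reason to expect it. The efficacy aim is also exploratory.
- **'Within-group' is undefined.** Clinic therapy groups also exist in this trial. Study arm is the natural reading, since the same section compares the intervention and wait-list groups. A clinic-group mean would have the same fault.
- **The participant's own mean is also an estimate.** Someone who answered 3, 3, 3 might have given a 4 to the skipped item. But that person's answers remain better evidence than the group's.

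None of this supplies a reason to prefer the group mean.

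**Conclusion.** The point holds in a conditional form. The stated rule ignores the participant's own answers. On AIM, IAM and FIM it can convert a neutral participant (sum 9, group mean above 3) or a mildly negative one (sum 8, group mean above 4) into a positive rating, and in any plausible result it errs only in the intervention's favour. Each case is worth 5 points on a proportion out of 20.

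How often this happens depends on an item-missingness rate that the article does not give. Under the illustrative assumptions, the chance per scale runs from 7–8% at 1% missing to 44–47% at 10%.

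The effect on the secondary scales is negligible at light missingness and material only at heavy missingness. Those figures assume eight items, correlation 0.6, missingness unrelated to the score and an unadjusted comparison. The mechanism is certain; a material effect on this trial's results is not. The change is worth making chiefly for the primary cutoff.

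**What to change.** Replace the imputation sentence with: 'If fewer than 40% of items are missing, the scale is scored from the participant's own answered items (person-mean, or response-pattern scoring for PROMIS); no group means are used.' Apply it to AIM, IAM, FIM and all secondary multi-item scales.

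Under this rule, answers of 3, 3, 3 score 3.00 and answers summing to 8 score 2.67, so both stay not positive. The 40% limit is unchanged.

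The cost is one sentence, with no new data and no extra participants. The article says that the analysis has yet to be carried out, so the change can be made before results are known.
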